### Voxel-base morphometry analysis

The gray matter volume (GMV) will be calculated using voxel-base morphometry (VBM) analysis in the FMRIB software library (FSL) (Jenkinson et al., 2012) version 5.0.9.^1^ First, all T1-weighted data will undergo brain extraction using the Brain Extraction Tool (BET) (Smith, 2002) and will be visually checked by an experienced neurologist to remove any leftover non-brain tissue. Second, using the FMRIB’s Automated Segmentation Tool (FAST) (Smith, 2002), the obtained brain-extracted data will be segmented into gray matter (GM), white matter (WM), and cerebrospinal fluid (CSF). Third, the resulting GM images were non-linearly registered to the GM ICBM-152 template using the non-linear registration tool FNIRT, and then averaged and flipped along the x-axis to obtain a first-pass, study-specific GM template. Next, the native segmented GM images will be nonlinearly re-registered to the above GM template and averaged to generate the final symmetric, study-specific GM template. Furthermore, the registered GM images will undergo modulation using the Jacobian of the warp field to produce maps of GMV. Finally, the obtained GMV images will be smoothed with a Gaussian kernel of 3 mm (a full-width half-maximum of ∼7 mm).

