## Methods

### Study design

This randomized clinical trial was designed to evaluate the treatment effect and neurological mechanisms of CAT on MWoA. A total of 96 female MWoA participants and 30 female healthy controls (HCs) will be enrolled. The study will last 20 weeks including a 4-week screening phase (week −4 to week 0), an 8-week treatment period (weeks 1–8), and an 8-week follow-up period (weeks 9–16). The enrollment schedules, interventions, and assessments are summarized in Table 1. During the screening phase, participants will be assessed headache diaries. Clinical outcomes will be evaluated after treatment and during the follow-up. Multimodal MRI scans will be performed at baseline and after treatment. A study flowchart is presented in Figure 1.

**TABLE 1 T1:** Study schedule for data measurements.

	Study period					
	Enrolment	Allocation	Treatment phase		Follow-up	
Timepoint	−4 week	0 week	4 week	8 week	12 week	16 week

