### Interventions

Healthy controls will not undergo any treatment during the trial period, brain imaging data will be collected only once. Based on Traditional Chinese Medicine (TCM) theory, which suggests that most migraines are associated with temporal headaches, and following the findings from our previous studies on acupuncture for MWoA (Li et al., 2022, 2023), we have selected six frequently used acupoints along the Shaoyang meridian. These acupoints include Fengchi (GB20), Shuaigu (GB8), Waiguan (TE5), Zhongzhu (TE3), Yanglingquan (GB34), and Zulinqi (GB41). The positioning of these acupoints will be determined according to the standards set by the WHO Standard Acupuncture Point Locations in the Western Pacific Region (2008) (WHO Regional Office for the Western Pacific, 2008). Locations of the acupoints are presented in Table 2 and Figure 2. The interventions are compliant with the Consolidated Standards of Reporting Trials (Schulz et al., 2010) and the Standards for Reporting Interventions in Clinical Trials of Acupuncture (MacPherson et al., 2002). Patients will be instructed to assume a prone position with the head and face down, thus obscuring their vision during the acupuncture procedure. Then, the acupuncturist will routinely disinfect the skin around the acupoints.

**TABLE 2 T2:** Location of acupoints.

Acupoints	Location
GB20 (Fengchi)	In the anterior region of the neck, inferior to the occipital bone, in the depression between the origins of sternocleidomastoid and the trapezius muscles.
GB8 (Shuaigu)	On the head, directly superior to the auricular apex, 1.5 B-cun superior to the temporal hairline.
TE5 (Waiguan)	On the posterior aspect of the forearm, midpoint of the interosseous space between the radius and the ulna, 2 B-cun proximal to the dorsal wrist crease.
TE5 (Waiguan)	On the posterior aspect of the forearm, midpoint of the interosseous space between the radius and the ulna, 2 B-cun proximal to the dorsal wrist crease.
GB34 (Yanglingquan)	On the fibular aspect of the leg, in the depression anterior and distal to the head of the fibula.
GB41 (Zulinqi)	On the dorsum of the foot, distal to the junction of the bases of the fourth and fifth metatarsal bones, in the depression lateral to the fifth extensor digitorum longus tendon.

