### Sample size calculation

Regarding the sample size calculation for the modulation of brain functional networks by acupuncture, there is no established method. However, in line with the requirements of brain functional network analysis techniques (Bossier et al., 2020), a sample size of 30 cases per group should provide relatively stable reproducibility. We plan to include 30 cases in each treatment group, and with an estimated loss rate of 8%, we will aim for 32 cases per group, resulting in a total of 96 cases. The HCs group will consist of 30 cases, as they are undergoing examinations only once and are generally not participants in loss.

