### MRI data

Magnetic resonance imaging data will be acquired within 1 week before the treatment and within 1 week after 8 weeks of treatment. The MRI will be acquired to avoid the patient’s migraine attacks, and all migraine patients should be without migraine (intermittent) for at least 72 h prior to the MRI scan before the scan is performed. Otherwise, the scan will be rescheduled. A Magnetic Resonance Scanner (3.0T GE Discovery 750; Milwaukee, WI, USA) with a 16-channel phased array head coil will be used, along with a restraining foam pad to minimize head motion and diminish scanner noise. The scans will be conducted at the Department of Radiology, the First Affiliated Hospital of Kunming Medical. Three-dimensional T1-weighted structural images will be obtained with the following scanning parameters: repetition time (TR) = 8.2 ms; echo time (TE) = 3.18 ms; field of view (FOV) = 256 mm × 256 mm; matrix = 512 × 512; in-plane resolution = 0.5 mm × 0.5 mm; slice thickness = 1 mm; 196 sagittal slices; flip angle = 9°. Resting-state functional MRI (rsfMRI) data will be collected within 7 min using the following parameters: TR = 2 s; TE = 30 ms; FOV = 240 mm × 240 mm; matrix = 64 × 64; in-plane resolution = 3.75 mm × 3.75 mm; slice thickness = 3.5 mm; 45 axial slices; flip angle = 90°, and 210 volumes will be acquired for each participant. Additional MRI data acquisition and preprocessing methods and procedures are described in Supplementary File 6.

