### Neuroimaging data analysis

The structural MRI data will be analyzed using the VBM toolbox within SPM12. The steps will include interlaminar time difference correction, spatial difference correction, head motion correction, normalization, and Gaussian smoothing (Yao et al., 2021). During head motion correction, images of participants with translations of less than 1 mm and rotational movements of less than 2° will be involved in the subsequent analysis. The MRI data will be analyzed using PANDA, GRETNA and BrainNet Viewer toolboxes and SurfStat. In VBM analysis, generalized linear regression model analysis will be used and between-group VBM comparisons will be made using corrected subject migraine attack intensity, migraine attack frequency, etc. (control covariates: age, PSQI, SAS, SDS, etc.) and total intracranial volume by two-sample *t*-test. A significant difference between groups will be indicated when *p* < 0.05 (FWE corrected). Only collections with more than 20 voxels will be considered as statistically significant brain regions. First, the FC of PAG in the baseline session will be compared between the migraine patients and normal participants using two sample *t*-test with FWE correction. Second, two-factor three-level mixed design ANOVA (Time: baseline and after treatment; Treatment: CAT, IAT, and sham CAT) will be conducted on migraine patients to explore the effect of treatment schedule on the FC of PAG after FWE correction. *Post hoc* analysis will be implemented using paired *t*-test to investigate the alteration of FC between before and after treatment for each treatment schedule. Finally, Pearson correlation analysis will be performed between the change in VAS score and the changes of FC in significant regions for three treatment schedules, respectively. The statistical analysis for the VBM will follow a similar procedure to that for the FC of PAG.

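### The grey-matter template, as described, averages unbalanced scans (patients outnumber controls about 6 to 1, or 3 to 1 at baseline only), and no within-patient registration step is shown before 8-week change is analysed

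*Protocol article*

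**What the plan says.** All points are in the protocol article.

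- **Scans available.** Study design: "A total of 96 female MWoA participants and 30 female healthy controls (HCs) will be enrolled". MRI data: "Magnetic resonance imaging data will be acquired within 1 week before the treatment and within 1 week after 8 weeks of treatment". For the controls, Interventions says "brain imaging data will be collected only once".
- **Template.** Voxel-base morphometry analysis gives an ordered FSL pipeline that opens with "First, all T1-weighted data will undergo brain extraction using the Brain Extraction Tool (BET". The images are then segmented. The grey-matter images are registered to a standard template, averaged and flipped to give a first-pass template. After that, "the native segmented GM images will be nonlinearly re-registered to the above GM template and averaged to generate the final symmetric, study-specific GM template". The registered images are modulated by the Jacobian of the warp and smoothed.
- **Use of the maps.** Neuroimaging data analysis compares patients with controls at baseline on PAG connectivity. It then fits a mixed ANOVA with Time and Treatment, followed by paired t-tests within each arm. It adds: "The statistical analysis for the VBM will follow a similar procedure to that for the FC of PAG".
- **Software.** Voxel-base morphometry analysis names FSL 5.0.9. Neuroimaging data analysis places the structural analysis in the VBM toolbox of SPM12.
- **Detail held elsewhere.** MRI data refers further acquisition and preprocessing detail to Supplementary File 6, which is not shown.

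**The concern.** There are two separate issues, and they affect different contrasts.

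**Template composition.** A study-specific template is the average of the images that go into it. If most come from patients, the average lies closer to patient anatomy, and controls may need larger warps to reach it. Grey-matter volume is modulated by the Jacobian of that warp, so a difference in registration accuracy between the groups can pass into the maps being compared. At stake is the baseline patient-control contrast, which is meant to show migraine-related structure. If both sessions enter, post-treatment scans also help to define the space in which a baseline contrast is tested.

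**Processing of the two sessions.** The images registered to the group template are the native ones, each with its own segmentation and warp. As listed, 8-week change is the difference between two separately estimated maps. Pairing in the statistical model removes stable differences between patients. It does not remove processing error specific to one scan. At stake is the precision of the Time by Treatment analysis, with about 30 evaluable patients per arm.

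**Working it through.** **Inputs.** 96 patients and 30 controls (Study design); two sessions per patient (MRI data); one per control (Interventions); 30 evaluable per arm, as in "We plan to include 30 cases in each treatment group", with 8% loss and 32 enrolled (Sample size calculation).

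**The plan's own figure.** The article states no patient-to-control scan ratio. The figure it does give is 32 per arm: 30 × 1.08 = 32.4, rounded to 32, and 3 × 32 = 96. (Dividing instead gives 30 / 0.92 = 32.6, or 33, a difference of one patient per arm.) The enrolment numbers are used as stated.

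**Template composition.** Ratio = patient images / control images; share = patient images / all images.

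| Scans averaged | Patients : controls | Ratio | Patient share |
|---|---|---|---|
| All, 96 × 2 | 192 : 30 | 6.4 | 192/222 = 86.5% |
| 96 baseline + 90 post-treatment | 186 : 30 | 6.2 | 186/216 = 86.1% |
| Completers, 90 × 2 | 180 : 30 | 6.0 | 180/210 = 85.7% |
| Baseline only, 96 | 96 : 30 | 3.2 | 96/126 = 76.2% |
| Baseline only, 90 completers | 90 : 30 | 3.0 | 90/120 = 75.0% |
| Balanced, 10 per arm + 30 controls | 30 : 30 | 1.0 | 50% |

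The imbalance is present on every reading of the text. Restricting to baseline halves it without removing it.

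**Between arms.** Each arm supplies 32 × 2 = 64 images if complete, or 30 × 2 = 60 with planned completers. The template is not tilted toward any arm.

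**Precision of change (illustration only).** Let σ² be the between-patient variance and r the scan-rescan correlation without registration error, so that Var(change) = 2σ²(1 − r). Suppose separate processing adds an independent error of variance fσ² to each scan. The variance of change is then multiplied by [2(1 − r) + 2f] / [2(1 − r)] = 1 + f/(1 − r).

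- r = 0.80, f = 0.02: 1 + 0.02/0.20 = 1.1
- r = 0.90, f = 0.05: 1 + 0.05/0.10 = 1.5
- r = 0.98, f = 0.10: 1 + 0.10/0.02 = 6.0

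Both r and f are assumptions; neither appears in the article. A range of 1.1-fold to 6-fold gives the direction of the effect but no usable estimate of its size.

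**The case against.** The strongest reply is that much of this is inferred from a condensed article. Four stronger readings are tempting, and the article supports none of them.

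- **That every scan is stated to enter the template.** All T1 data are the stated object of brain extraction. The averaging sentences do not name the sessions. Averaging everything is the natural reading but is not explicit. A second scan of the same person also adds little new anatomy, so counted by persons the ratio is 3.2 to 1. This stands, and is why both ratios are reported.
- **That the two scans are treated as unrelated.** Statistically they are paired, through the Time factor and the paired t-tests. The point concerns image processing only, and Supplementary File 6 could contain a within-patient step. Even so, the article lists its steps from brain extraction to smoothing and says that native images are registered to the group template. The step list given with SPM12 shows no within-patient registration for structural change either. An added step would have to be reconciled with that text.
- **That the patient-control contrast is shown to be biased.** It is not. Both groups share sex, handedness, age range and education level, and intracranial volume is adjusted for. A large mismatch is not evident. Intracranial volume is a global measure, however, and does not correct local registration accuracy. Jacobian modulation accounts for volume change during warping but also carries any error in the warp. The risk is possible, with no known size.
- **That the loss equals a stated number of patients per arm.** Such a conversion rests wholly on assumed correlations. Errors driven by anatomy are also partly shared between a patient's two scans, and cancel in the difference.

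Finally, since two packages are named for the same analysis, it is not settled that the FSL template will be the one used. That limits the template point to the FSL pipeline, and is itself something to correct.

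**Conclusion.** The point holds as a cheap improvement to the stated method. As described, the template is unbalanced: about 6 to 1 if both patient sessions enter (6.0 to 6.4) and about 3 to 1 if only baseline scans do (3.0 to 3.2). This could make registration accuracy unequal in the baseline patient-control grey-matter contrast.

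A reader might infer that the randomised comparison is compromised. It is not biased by this, because CAT, IAT and sham CAT contribute equally to the template. The primary outcome, VAS attack intensity, is unaffected.

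The absence of within-patient registration in the listed steps can cost precision in the pre-post grey-matter analysis. The size of that cost cannot be computed from the article. The conclusion assumes that the FSL pipeline is used as written and that Supplementary File 6 does not add balancing or a longitudinal step.

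**What to change.** 1. State one VBM pipeline. Reconcile FSL 5.0.9 in Voxel-base morphometry analysis with SPM12 in Neuroimaging data analysis, and check both against Supplementary File 6.
2. State which scans form the template, and build it from equal numbers of controls and baseline patient scans: for example, the 30 controls and 30 patients, 10 from each arm, chosen by a rule fixed in advance. Register all scans to that template.
3. For the Time by Treatment analysis, register each patient's two scans to a within-patient midpoint and derive grey-matter change there, before normalising to the group template. If Supplementary File 6 already contains such a step, say so in the main text and amend the wording about native images.

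No new scans are needed. The cost is revised wording, some extra computing, and fewer images in the template (60 instead of up to 222).

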### Clinical data analysis

Statistical analysis will be performed by independent statisticians who will have no knowledge of group allocation or the intervention process. Clinical outcomes will be analyzed using SPSS 28.0 statistical software (SPSS Inc., Chicago, IL, USA). All statistical analyses will adhere to the intention-to-treat principles. The missing data of participants who drop out will be handled using multiple imputation by chained equations (Azur et al., 2011), which can impute mixtures of continuous, binary, unordered categorical, and ordered categorical data. In addition, a per-protocol population analysis will be performed on participants who have completed at least 80 percent of their treatment protocol after randomization. Qualitative data will be presented as percentages [*n* (%)] and compared using the Chi-square (χ^2^) test. Quantitative data will be reported as means ± SDs and IQRs. Shapiro–Wilk tests will be performed to assess the normality of the data. Comparisons among the three groups will be analyzed using one-way analysis of variance (ANOVA), and non-parametric tests will be employed when the distribution is not normal. Outcomes will be analyzed using a one-way repeated measures ANOVA to evaluate the impact of time, group, and time × group interactions on migraine attacks. Comparisons of categorical data among groups will be examined using χ^2^ tests or Mann–Whitney U tests. All hypothesis tests will be two-tailed analyses, with statistical significance determined by a *p*-value < 0.05.

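### Imputation is limited to participants who drop out, but the repeated-measures ANOVA needs complete rows, so intention-to-treat is not secured for retained participants with an intermittent missing assessment

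*Protocol article*

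**What the plan says.** Three statements in the protocol article, Methods, Clinical data analysis, have to be read together.

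- Principle: "All statistical analyses will adhere to the intention-to-treat principles".
- Missing data: "The missing data of participants who drop out will be handled using multiple imputation by chained equations". No other rule for missing clinical data is given.
- Longitudinal test: "Outcomes will be analyzed using a one-way repeated measures ANOVA to evaluate the impact of time, group, and time × group interactions on migraine attacks". It is called one-way, but with group, time and their interaction it is a mixed between-within design.

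The same section names the software ("Clinical outcomes will be analyzed using SPSS 28.0 statistical software") and adds a secondary analysis set: "a per-protocol population analysis will be performed on participants who have completed at least 80 percent of their treatment protocol after randomization". It does not mention missed assessments in participants who remain in the trial. It also does not say that such participants are to be excluded.

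Table 1 schedules the diary and six questionnaires at weeks 0, 4, 8, 12 and 16. The Primary outcome section has patients fill in the diary by hand after each attack, and a researcher collects it every 4 weeks.

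**The concern.** A classical repeated-measures ANOVA works on one row per person with every occasion filled. A single empty cell removes the whole row, including the values that were observed. The imputation sentence fills the rows of people who leave the trial. It does not, as worded, fill the row of someone who stays and misses one 4-week return or one questionnaire. Taken literally, a participant lost at week 6 is analysed, while one who attended throughout but missed week 12 is not.

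Two things are at stake. The first is precision in a trial with 32 per arm. The second is that the analysed set would depend on something that happens after randomisation, namely having a value at every assessment, and intention-to-treat is meant to prevent that. The article gives no evidence that completeness would differ between arms, so a bias is possible but not shown.

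Gaps of this kind are plausible with a paper diary and repeated questionnaires over 16 weeks. A diary period without any attack would also have no intensity entry. The article does not say how that is scored, and I do not count it in the figures below.

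**Working it through.** **The plan's own figure.** The Sample size calculation section allows for 8% loss on 30 per group and arrives at 32 per group, 96 in total. Dividing, 30 / 0.92 = 32.6, which rounds up to 33. The stated 32 is one below that, and 3 × 32 = 96. Expected completers are 32 × 0.92 = 29.4 per arm against the target of 30, so there is no reserve. This 8% concerns participants who leave, whom the plan imputes. It is not the loss examined here.

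**Inputs.**
- Participants per arm: 32 (Sample size calculation).
- Post-baseline assessments: 4, at weeks 4, 8, 12 and 16 (Table 1).
- Baseline is treated as complete: headache intensity in the baseline period is an inclusion criterion, and Table 1 places the questionnaires at week 0, when randomisation takes place.
- Share of values missing at each post-baseline assessment in retained participants, q: not in the documents. Assumed 2% to 5%, with misses independent between assessments.

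**Formula.** Share of complete rows = (1 − q)^4. Rows lost per arm = 32 × [1 − (1 − q)^4].

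| q (assumed) | Complete rows | Lost of 32 per arm | Kept of 96 |
|---|---|---|---|
| 2% | 0.98^4 = 0.922 | 2.5 | 88.5 |
| 5% | 0.95^4 = 0.815 | 5.9 | 78.2 |

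**Sensitivity of these figures.**
- If the planned 8% drop-outs have all their gaps imputed, only the 29.44 retained per arm are exposed. The loss is then 29.44 × 0.078 = 2.3 to 29.44 × 0.185 = 5.5 per arm.
- If gaps up to week 8 are all recovered, because patients attend three times a week until then, only weeks 12 and 16 are exposed. The loss is 32 × (1 − 0.98^2) = 1.3 to 32 × (1 − 0.95^2) = 3.1 per arm.
- If misses cluster in the same people, fewer rows are lost at the same q.
- If imputation covers every missing outcome value, no row is lost.

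**Can the ANOVA be combined with imputation?** Yes. A simulation of 400 trials with no treatment effect used 32 per arm, five occasions, correlation 0.5, 8% drop-out, 5% intermittent gaps and 20 chained-equation imputations of all gaps. The joint group × time test was pooled with the standard multi-parameter rule (D1) in every trial. It rejected in 0.0675 of trials, or 0.0575 with the denominator degrees of freedom capped at 93, against a nominal 0.05. The Monte Carlo standard error is √(0.05 × 0.95 / 400) = 0.011.

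**The case against.** The strongest reply is that this leans on one phrase in a condensed article. The article never says that incomplete cases are deleted. Chained equations run on the whole data set would fill intermittent gaps as well. Drop-out is the only loss the protocol quantifies, and it is imputed. Frequent attendance to week 8 and regular monitoring of the diaries should keep other gaps few. Part of this stands: the size of the problem is unknown and may be small. It does not remove the mismatch, because the article states a scope for imputation, and that scope is narrower than the named test requires.

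A reader might also infer four stronger points, which the documents do not support.

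- *The ANOVA cannot be pooled over imputed data sets.* It can, by standard rules for multi-parameter tests. The article names no combination rule, but that is commonly left to the statistical analysis plan.
- *Intention-to-treat is not delivered at all.* Drop-outs are imputed and enter the test with complete rows. The shortfall concerns retained participants with gaps.
- *All measures at all visits must be imputed jointly, too many columns for 96 patients.* No joint model is stated, and each outcome can be imputed separately.
- *The loss comes on top of the 8% drop-out.* Imputed drop-outs are not lost from this analysis, so the two do not add up.

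**Conclusion.** The point holds in a limited form. Following the section as written, a retained participant with one missing assessment is neither imputed nor kept in the repeated-measures ANOVA, contrary to the intention-to-treat statement beside it. At an assumed 2% to 5% missing at each of four post-baseline assessments, about 2.5 to 6 of 32 per arm would be lost from the test. This rests on a complete baseline, independent misses, a literal reading of the imputation sentence, and a rate that the documents do not give. Under the milder assumptions shown above the loss is smaller. It is a moderate defect in the stated analysis that wording can repair, and it should be settled before the data are unblinded.

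**What to change.** Preferred: make a likelihood-based mixed model for repeated measures the main analysis of the longitudinal outcomes.

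- Terms: arm, visit, arm × visit, and the baseline value as covariate.
- Unstructured covariance, fitted by REML.
- All randomised participants and all observed visits, with the arm contrasts taken from the model.
- Chained-equation imputation kept as a sensitivity analysis and applied to all missing outcome values. This also covers anyone without a post-baseline value, who adds nothing to the arm contrasts in the mixed model.

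Minimum alternative: keep the ANOVA, replace the restriction to drop-outs by all missing outcome values, and pool the arm contrasts over the imputed data sets. This alone closes the gap.

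Both routes ordinarily assume that data are missing at random, so the choice between them does not change that assumption. The cost is analysis wording. The software already named can fit the mixed model. The small downside is that its covariance structure must be fixed in advance.

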### Randomization and blinding

All MWoA participants will be randomly assigned in a 1:1:1 ratio to one of three groups: Group A (CAT group), Group B (IAT group), and Group C (sham CAT group). Random numbers will be generated using a computer and sealed in opaque envelopes by an independent research assistant. After acceptance of the random allocation principle, participants will randomly select an opaque envelope to receive an allocation serial number, which will be recorded on a Case Report Form (CRF) by a dedicated research assistant. To maintain blinding, the researchers, assessors, and statistical analysts will be separated throughout the study. Due to the specific nature of the sham acupuncture operation, it will be difficult to blind the acupuncturists during the treatment. They will receive training from the investigator and will be instructed not to disclose the allocation of participants unless there are exceptional circumstances, such as severe infection or uncontrollable pain. During treatment, participants will be accommodated in separate rooms to minimize communication.

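### A Shapiro–Wilk test on the trial's own data chooses between means and ranks for each three-group comparison, so the quantity tested is not fixed in advance

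*Protocol article*

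**What the plan says.** All the relevant text is in the Clinical data analysis section of the protocol article.

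- The check: "Shapiro–Wilk tests will be performed to assess the normality of the data".
- The default: "Comparisons among the three groups will be analyzed using one-way analysis of variance (ANOVA").
- The fallback, in the same sentence as the default: "non-parametric tests will be employed when the distribution is not normal".
- A separate sentence, with no normality condition: "Outcomes will be analyzed using a one-way repeated measures ANOVA to evaluate the impact of time, group, and time × group interactions on migraine attacks".

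The fallback test is not named. Nor is the Shapiro–Wilk cut-off, or what is tested: raw values or residuals, by arm or pooled, by visit or overall. The section sets two-sided testing at 0.05 for all hypothesis tests. It does not say whether the one-way comparison or the repeated-measures ANOVA decides the primary outcome, which the Primary outcome section defines as attack intensity on a 0–10 VAS.

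**The concern.** One-way ANOVA asks whether mean VAS, or mean attacks per month, differs between arms. A rank test asks whether values in one arm tend to be higher than in another. When a preliminary test on the outcome data chooses between them, the question put to each outcome is settled only after the data are in, and it can differ from outcome to outcome for reasons unrelated to treatment.

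Three consequences follow.

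1. After a switch, the test no longer refers to a difference in VAS points or attacks per month. The Introduction says the trial should inform the choice between contralateral and ipsilateral acupuncture, and that choice needs an effect size.
2. A rank-based p-value would stand beside a mean-based repeated-measures analysis of the same outcome, with no ranking between the two.
3. The same section plans multiple imputation. A Shapiro–Wilk result can differ between imputed datasets, and an omnibus rank test gives no estimate with a standard error to pool.

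**Working it through.** **Inputs from the protocol.** "All MWoA participants will be randomly assigned in a 1:1:1 ratio to one of three groups" (Randomization and blinding). "We plan to include 30 cases in each treatment group", then "with an estimated loss rate of 8%, we will aim for 32 cases per group, resulting in a total of 96 cases" (Sample size calculation). Two-sided 0.05 (Clinical data analysis).

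**The plan's own figure.** 30/0.92 = 32.6 per arm, against the stated 32. In the other direction, 32 × 0.92 = 29.4 completers. About 30 per arm is therefore the right size for the check. The protocol gives no power, effect size or SD to reproduce.

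**Assumptions, because the protocol is silent.** Shapiro–Wilk cut-off 0.05; Kruskal–Wallis as fallback; VAS SD 1.5, with arm means 1.0, 0.5 and 0 apart when there is an effect; attack counts gamma-Poisson with mean 4, frailty shape 2 or 4, and reductions of 1/3, 1/6 and 0.

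**Step 1: switching by chance under exact normality.** If each arm is tested and any failure triggers the switch, the probability is 1 − 0.95³ = 1 − 0.857 = 14.3%, and simulation agrees (14%). If pooled residuals are tested once, it is about 5%.

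**Step 2: switching under plausible shapes (simulated, 30 per arm unless stated).**

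| Outcome | Any arm fails | Pooled residuals fail |
|---|---|---|
| Exactly normal | 14% | 5% |
| VAS to one decimal (mean 3.5, SD 1.8, 32 per arm) | 12.5% | 6.6% |
| VAS in whole numbers (SD 1.5) | 83% | 37% |
| Attack counts | about 96–100% | almost always |

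For VAS, the choice of test depends heavily on how scores are recorded or averaged and on what is tested. The protocol does not fix what is tested.

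**Step 3: does the choice change the result?** ANOVA and Kruskal–Wallis fall on different sides of p = 0.05 in about 7% of VAS trials (at about 60% power) and about 10% of count trials. With no effect, and 32 per arm, they disagree in 1.9% to 3.4% of trials.

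**Step 4: type I error.** The two-step rule gave 0.045 to 0.053 at nominal 0.05 with 32 per arm, and stays near 5% with 30 per arm. There is no material inflation.

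**Step 5: power lost by switching to ranks for counts.** Kruskal–Wallis against ANOVA gave 29% against 32% (frailty shape 2) and 40% against 42% (shape 4), so the loss is about 2 to 4 points allowing for simulation error. Adding the baseline count to a linear model raised power to 48% and 53%. That gain comes from baseline adjustment, not from avoiding ranks.

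**Step 6: what the switch covers.** The fallback clause sits in the sentence on comparisons among the three groups. The repeated-measures sentence follows it and is unconditional. Read literally, a failed normality test changes the first analysis and leaves the second in place.

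**The case against.** The strongest reply is that the rule is stated in advance, is applied by statisticians unaware of allocation, and keeps its type I error, so it is not opportunistic. All of that stands, and it is why this is not a false-positive problem. For counts the switch is nearly certain, so their test is in effect fixed; the instability mainly affects VAS and scale scores. Disagreement between the tests means p-values either side of 0.05, not opposite directions of effect. Means, SDs and IQRs are reported whatever the normality result, so a reader could subtract arm means. That difference would still not be what the rank test assesses, and it would carry no interval from that test.

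It is also fair that a condensed article may leave the cut-off and the unit tested to a fuller document. Their absence is not the point. The stated rule is the point, and a later plan would have to overturn it rather than fill it in.

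Some stronger readings are tempting but unsupported:

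- A reader might infer that a switch leaves the time × group question without an analysis. It does not, because the repeated-measures ANOVA has no normality condition. Only if the fallback were read onto that sentence would a named alternative be lacking.
- A reader might count a failure in any arm at any visit as a switch and arrive at a much higher chance rate. No such rule is stated.
- A reader might take the check to be on raw values. That is a natural reading, but it is not explicit.
- A reader might blame the rank test for low power on counts. Step 5 shows that most of the gap to a baseline-adjusted model comes from the baseline adjustment.

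**Conclusion.** The point holds for the three-group comparisons. Whether each is made on means or by an unnamed non-parametric test is left to a normality test on the trial's own data. By chance alone the switch occurs in about 5% to 14% of trials per outcome. It occurs in about 37% to 83% for whole-number VAS, close to the chance rate if VAS is effectively continuous, and almost always for attack counts. The choice moves a result across p = 0.05 in about 7% to 10% of trials with a real effect.

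The harm is an unfixed target of inference, no direct effect estimate after a switch, and two unranked analyses of VAS. It is not alpha inflation, and no planned analysis is lost. The percentages rest on the assumed cut-off, fallback test and outcome shapes; that the quantity tested is not fixed in advance follows from the text alone. This is a cheap improvement worth making before unblinding, not a fault that invalidates the trial.

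**What to change.** Delete the normality switch and fix one analysis per outcome:

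- VAS and scale scores: a baseline-adjusted linear or mixed model on means.
- Attack frequency and attack days: a baseline-adjusted count model, for example negative binomial.
- Primary outcome: state that the VAS model, at a named time point, decides it, and give the repeated-measures ANOVA a supporting role or replace it with that model.
- Reporting: arm differences (or rate ratios for counts) with 95% confidence intervals for every outcome.
- Rank tests: report them as sensitivity analyses whatever the normality result.

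These models also give estimates that can be pooled under the planned multiple imputation. The cost is a few sentences and minor programming. The downside is slightly lower power than a rank test for a very skewed scale, which the sensitivity analysis would show.
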